# Efficacy of *Banha-sasim-tang* on functional dyspepsia classified as excess pattern: study protocol for a randomized controlled trial

**DOI:** 10.1186/s13063-017-2282-z

**Published:** 2017-11-09

**Keywords:** Functional dyspepsia, *Banha-sasim-tang*, Excess pattern, Randomized trial

## Abstract

**Background:**

Functional dyspepsia (FD) refers to the presence of one or more gastrointestinal symptoms including postprandial fullness, epigastric pain, burning, and early satiety without an organic explanation for chronic symptoms. FD causes considerable discomfort in patients and affects their everyday activity and productivity. Because most conventional treatments have limited efficacy, numerous patients seek alternatives such as herbal medicines. In this proposed study, we will conduct a clinical trial of an herbal drug, *Banha-sasim-tang* (BST). Furthermore, participants will be limited to those classified as having an excess pattern by using an instrument of pattern identification for FD to determine the efficacy of BST in a specific subset of patients.

**Methods:**

This randomized, blinded, parallel-group clinical trial of BST versus placebo will consist of 4 weeks of oral administration of BST or placebo and a 4-week follow-up period. The Korean version of the symptom-based questionnaire of the Nepean Dyspepsia Index (NDI-K) will be used as the primary outcome measure. Secondary outcome measures will include the quality-of-life (QoL) evaluation from the NDI-K, the FD-related QoL (FD-QoL) scale, assessment of gastric myoelectrical dysrhythmias (GMA), and a Visual Analog Scale (VAS) analysis.

**Discussion:**

The results of this trial are expected to provide relevant evidence demonstrating that BST can be used as an effective treatment in a specific subset of FD subjects.

**Trial registration:**

KCT 0002013. Registered at Clinical Research Information Service in the Republic of Korea on 18 August 2016.

**Electronic supplementary material:**

The online version of this article (doi:10.1186/s13063-017-2282-z) contains supplementary material, which is available to authorized users.

## Background

Dyspepsia, which is characterized by the presence of one or more of the following symptoms, postprandial fullness, epigastric pain, burning, and early satiety, is thought to originate in the gastroduodenal region of the upper gastrointestinal (GI) tract [1]. Studies using upper GI endoscopy have indicated that less than 10%, less than 1%, and more than 70% of patients with dyspepsia had a peptic ulcer, gastroesophageal cancer, and functional dyspepsia (FD), respectively [2]. The chronic symptoms of FD have no organic explanation, occur at least weekly, and last for at least 6 months [3]. The global prevalence of FD is between 5 and 11%, and 40% of patients visit a physician for medication owing to considerable discomfort and detrimental effects on everyday activities and productivity [4–6]. Unfortunately, conventional medicines have limited efficacy, and up to 50% of patients with FD seek alternative treatments such as herbal medicines [5].

*Banha-sasim-tang* (BST, *Banxia-xiexin-tang* in traditional Chinese medicine and *Hange-shashin-to* in *Kampo* medicine) is an herbal formula containing the following seven herbs, *Pinelliae* tuber, *Scutellariae radix*, *Zingiberis rhizoma*, *Ginseng radix*, *Glycyrrhizae radix*, *Zizyphi fructus*, and *Coptidis rhizoma*. It is used for the treatment of epigastric stuffiness which, in Korean medicine, is a disease state characterized by discomfort in the epigastric region [7]. The efficacy of BST for improving GI function and its mechanism of action have been elucidated in several studies [8–10]. In the light of the findings of these studies, the present proposed randomized, double-blind, placebo-controlled, clinical trial aims to investigate the efficacy of BST for the treatment of FD.

To date, two randomized controlled trials (RCTs) of the efficacy of BST on FD have been performed. The first study evaluated the efficacy of BST in patients with FD and cold-heat complexity pattern, whereas the other included patients with common FD. The first study indicated a significant improvement occurred in the treatment group over the placebo group, whereas the other study did not indicate a significant difference in the primary outcome between the treatment and the placebo groups [11, 12]. The discrepancy in these results was likely due to pattern features specific to a type of oriental medicine (traditional Chinese, *Kampo*, or Korean medicine practices).

Oriental medicine has, for 23 centuries, considered the human body to be a holistic system, and purports that the maintenance of health occurs via a balance of this system through a unity of opposites, mutual control, and the inter-transformation of substances and functions in the body [13, 14]. An imbalance in this dynamic equilibrium causes illness. Thus, the main principle of treatment is to restore balance and correct the functional manifestation of the imbalance, which is a key factor for diagnosis in oriental medicine. Different functional manifestations and signs, which are diverse owing to each patient’s constitution and individual state, are categorized under “patterns” (called “*Zeung*” in Chinese). Patterns have been used as diagnostic tools, and for determining acupoints and medicinal herbs for treatment in oriental medicine [13, 15]. Today, patterns are considered for designing clinical trials using medicinal herbs and acupuncture.

In the above theory, the patients with FD may have been classified into multiple “patterns” and, therefore, may have required pattern classification for treatment to be effective overall. Therefore, we will perform a clinical trial using BST specifically for the treatment of excess pattern, the accumulation or stagnation of metabolic waste, body fluids, and blood.

## Methods

### Study design

This trial is an investigator-initiated, randomized, blinded, parallel-group trial, in the Daejeon Oriental Hospital of Daejeon University in Daejeon, Korea, of BST versus placebo for patients with FD and excess pattern. This clinical trial will consist of 4 weeks of oral administration of BST or placebo and a 4-week follow-up period (Fig. 1). A Standard Protocol Items: Recommendations for Interventional Trials (SPIRIT) Checklist [16] is provided in Additional file 1.

**Fig. 1 Fig1:**
[figure not shown]
Flow chart of trial design and schedule

### Recruitment

Participants will be recruited through advertisements in our hospital and in local newspapers.

### Population

#### Inclusion criteria

The patient inclusion criteria are as follows:Age 19 to 75 years with persistent dyspepsia for over 3 years and an onset of symptoms of at least 6 months prior to study enrollmentNormal endoscopy within the previous 3 yearsMeet the ROME III criteria [17]:Persistent dyspepsia for over 3 months and one or more of the following symptoms: postprandial fullness, early satiety, epigastric pain or burning, and no evidence of structural disease (including in upper endoscopy) that likely explains the symptomsTwo or more of the following eight moderate symptoms: epigastric pain, discomfort, burning, stuffiness, and fullness, as well as postprandial fullness, nausea, and early satiety; and a total of at least 6 points in the scoring of the eight symptoms using the following severity scale: 0; mild: 1; moderate: 2; and severe: 3Referred with an excess pattern determined using an instrument of pattern identification for FD [18]Ability to provide fully informed consent to participate in the study

#### Exclusion criteria

The patient exclusion criteria are as follows:History of GI surgery (except appendectomy)Presence of GI bleeding, intestinal obstruction, or GI perforationConfirmed or likely (current or within the previous 2 years) colorectal cancer, duodenitis or stomach cancerSevere hepatic dysfunction, congestive heart failure, or renal failureLiver enzymes, AST or ALT, increased by two or more times over the normal rangeCurrent or past use of non-steroidal anti-inflammatory drugs (NSAIDs) or corticosteroidsUse of other investigational study drugs within 30 days before study entryWomen who are pregnant or lactating. Woman of child-bearing age must be using adequate contraceptionInability to complete relevant questionnaires

### Withdrawal, dropout, and discontinuation

Participants can voluntarily withdraw at any time during the trial, and the investigator can terminate the observation and exclude participant data if necessary. Reasons for withdrawal will be recorded in Case Report Forms (CRFs), and the last data recorded for these participants will be included in the data analysis. The trial can be terminated under the following circumstances: (1) occurrence of serious adverse events (AEs) related to the research medication, (2) at the request of the participants, (3) non-compliance to trial medication, and (4) the request for other medications to relieve the symptoms of FD.

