#### Concomitant medication

Medications that may affect the efficacy of the trial medication, including NSAIDs, corticosteroids, and GI motility-related drugs will be prohibited. Patients will receive treatment for severe symptoms immediately they occur. However, the patients can be excluded under the request for other medications to relieve the symptoms of FD.

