### Randomization

In this study, patient randomization will be performed with a group allocation ratio of 1:1. The random sequence will be generated using a computer-generated random number table, and random numbers will be assigned using sealed, opaque envelopes. Both the patients and clinicians will be blinded until the end of the trial. The research team involved in the treatment administration and data collection will not have a role in the assignment process.

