### Sample size calculation

The objective of this study is to validate the effect of BST treatment on FD. In this study, the sample size will be estimated based on the results of several clinical experiences and two previous studies [22, 23]. The average variation (*δ*) is assumed to be 20 and the standard deviation (SD = *σ*) is assumed to be 22.4 between the treatment and the placebo (control) groups. In addition, the patients will be allocated at a 1:1 ratio to each group and assessed a two-sided test after considering 5% significance and 80% power levels. Therefore, this study will include 40 participants, who will be divided into two groups of 20 (*n*) each:$$ n=\frac{2\times {\left({Z}_{\alpha /2}+{Z}_{\beta}\right)}^2\times {\sigma}^2}{\delta^2}. $$

Considering a potential dropout rate of 20%, this study will require at least 50 participants.

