**Table 1 Tab1:**
[figure not shown]
Schedule for enrollment, intervention, and assessment

*BST Banha-sasim-tang*, *ECG* electrocardiogram, *GMA* Gastric myoelectrical dysrhythmias, *FD-QoL* Functional dyspepsia-related quality of life, *NDI-K* Korean version of the Nepean Dyspepsia Index, *QoL* quality of life, *PA* posterior-anterior, *VAS* Visual Analog Scale

Data will be analyzed using the intention-to-treat analysis and will include all participants who will undergo randomization. The analysis will be performed considering each individual as a unit of analysis. All reported *p* values will be two-tailed and for each analysis, *p* < 0.05 will be considered statistically significant. Data will be described as the mean, standard deviation (SD) or frequency, percentage, and confidence interval (CI). Category-type data will be analyzed using the Pearson’s χ^2^ test or Fisher’s exact test. Measurement and rating data will be described using the Student’s *t* test and the Wilcoxon rank sum test, respectively. Missing data will be imputed using multiple imputations and the statistical analysis will be performed using the statistical analysis SAS software (version 9.4, SAS Institute Inc., Cary, NC, USA).

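### An open-ended power to exclude participant data conflicts with the stated intention-to-treat analysis of everyone randomised

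*Protocol article*

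**What the plan says.** Three sections of the protocol article bear on who enters the primary analysis.

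- **Withdrawal, dropout, and discontinuation.** After allowing voluntary withdrawal, it says that "the investigator can terminate the observation and exclude participant data if necessary". The following sentence, on withdrawals, says that "the last data recorded for these participants will be included in the data analysis". The section then lists four circumstances for termination. Two of them are non-compliance with trial medication and a request for other medication for dyspepsia symptoms.
- **Concomitant medication.** Here "the patients can be excluded under the request for other medications to relieve the symptoms of FD". The text does not say whether this means excluded from treatment, from follow-up or from the analysis.
- **Data collection and analysis.** "Data will be analyzed using the intention-to-treat analysis and will include all participants who will undergo randomization". It also says "Missing data will be imputed using multiple imputations".

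The Randomization section states that "Both the patients and clinicians will be blinded until the end of the trial". Nothing in the article limits the exclusion of data to a secondary or per-protocol set, defines when it is needed, or requires the decision before unblinding.

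**The concern.** A discretionary power to drop a randomised participant's data is incompatible with a primary analysis of all randomised participants. This is not a detail that an analysis plan could supply later: the article states both rules, and no plan could honour both.

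The primary outcome is change in the NDI-K symptom score, assessed at baseline, at weeks 2 and 4, and 4 weeks after treatment ends. Participants whose symptoms persist are plausibly the ones who ask for other medication. If exclusion under the Concomitant medication section reaches the analysis, or if the investigator's discretion is used for such patients, removal will track the endpoint. Even if only observation stops, later NDI-K scores are lost for participants who are not doing well, and imputation then has to model what could have been collected. In a trial of 50, a handful of such cases can move the result.

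**Working it through.** **Textual check.** Set side by side:

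| Section | Consequence for a participant taken off the trial |
|---|---|
| Withdrawal, dropout, and discontinuation, on the investigator's power | Data may be excluded; no criterion |
| Same section, next sentence | Last recorded data are analysed |
| Concomitant medication | May be excluded; object not stated |
| Data collection and analysis | Analysed as randomised; missing values multiply imputed |

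The first row conflicts with the second and the fourth. The third row fits either side, depending on what exclusion means.

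**The plan's own figure.** Inputs from Sample size calculation: "The average variation (*δ*) is assumed to be 20"; "the standard deviation (SD = *σ*) is assumed to be 22.4"; two-sided 5% significance, 80% power, 1:1 allocation, 20% dropout.

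n = 2 × (1.960 + 0.842)² × 22.4² / 20² = 19.69, rounded up to 20 per group, 40 in total. With dropout, 40 / 0.80 = 50. Both stated figures reproduce, so no number in the article is in error. By the normal approximation, power is 88.4% with all 50 analysed and 80.6% with 40.

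**Illustration of consequences.** The article gives no exclusion rate, so the number removed is an assumption and is shown as a range. Simulated trials have 25 per arm, normally distributed change scores with SD 22.4 (oriented so that higher means more improvement), and a two-sample t test at two-sided 5%. The poorest responders are deleted completely, with no retained or imputed data.

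*(a) Removal depends on outcome only, blind to arm:*

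| Removed of 50 | Type I error, no true effect | Mean estimate, true difference 20 | Power |
|---|---|---|---|
| 0 | about 5% | 20.0 | 87% |
| 2 | about 5% | 17.5 | 81% |
| 5 | about 5% | 15.1 | 71% |
| 10 | about 5% | 12.4 | 56% |

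With no true effect, both arms lose the same kind of patient and the comparison stays fair. With a true effect, the poorest responders sit mostly on placebo. Removing them raises the placebo mean, and the estimate shrinks by 2.5, 4.9 and 7.6 points.

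*(b) Removal from one arm only, no true effect:*

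| Removed of 25 in that arm | Spurious difference (points) | Type I error |
|---|---|---|
| 1 | 1.8 | about 7% |
| 2 | 3.4 | about 9% |
| 3 | 4.9 | about 13% |
| 5 | 7.5 | about 24% |

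Scenario (b) requires exclusion to depend on arm, not merely on outcome.

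**The case against.** **The surrounding text already protects the analysis.** The sentence after the exclusion clause keeps the last recorded data, and the analysis section adds intention-to-treat and multiple imputation. Read generously, the investigator may only end further observation. This carries weight: the intention to keep everyone is stated more than once. But the clause speaks of excluding data, which goes further than ending observation, and nothing cancels it. The retention sentence therefore makes the section inconsistent with itself.

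**The triggers are not tied to data exclusion.** Non-compliance and requests for other medication are listed as grounds for termination, not for removing data, and exclusion under Concomitant medication may mean only leaving the trial. This stands. The text permits outcome-related removal from the analysis; it does not prescribe it, and nothing shows that it has occurred.

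**Blinding limits the damage.** A reader might infer that outcome-driven exclusion destroys the 5% error rate whatever the blinding, or biases the result in either direction. The documents do not support that. Patients and clinicians are stated to be blinded, and arm-blind removal leaves type I error near 5% and pulls a beneficial effect towards zero. Inflation to between 7% and 24% needs exclusion that differs by arm, for example because blinding fails or tolerability differs. The 20% in the sample size section is an overall dropout allowance, not an exclusion rate for one arm.

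**Conclusion.** The concern holds as an internal contradiction about the primary analysis population. The article gives the investigator an unqualified power to exclude data, keeps withdrawn participants' last data in the adjacent sentence, and promises an analysis of everyone randomised. It leaves open what exclusion means for patients who request other medication.

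If the power were used on poor responders under intact blinding, the expected harm is a diluted effect and lost power, not false positives. Removing 5 of 50 would cost about a quarter of the assumed effect (15.1 against 20) and about 16 percentage points of power (71% against 87%). These figures assume complete deletion, perfect selection of the poorest scores and normal data. They are an illustration, not a forecast. Retaining last data or imputing, as the article also states, would change them.

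The sample size is unaffected. How retaining last recorded data fits with multiple imputation is a related but separate question.

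**What to change.** 1. In Withdrawal, dropout, and discontinuation, delete the clause that allows participant data to be excluded.
2. Reconcile that section with Concomitant medication and with Data collection and analysis, so that stopping treatment or participation is kept separate from removing data. State what exclusion refers to for patients who request other medication. When treatment stops is for the sponsor to decide and is not addressed here.
3. State that all randomised participants are analysed in their assigned arm, and that the NDI-K assessments already scheduled are still sought from those who stop early, unless consent is withdrawn.
4. Confine any exclusion to a labelled per-protocol sensitivity set, with its membership fixed before unblinding.

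The cost is protocol wording plus completing questionnaires already in the schedule. The number randomised stays at 50, and no new procedures are needed.

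### The withdrawal section lets the investigator exclude a randomised participant's data, which conflicts with its own next sentence and with the intention-to-treat analysis of everyone randomised

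*Protocol article*

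**What the plan says.** Three statements in the protocol article bear on whose data are analysed.

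- Methods, Withdrawal, dropout, and discontinuation: participants may leave at any time, and "the investigator can terminate the observation and exclude participant data if necessary".
- Same section, next sentence: reasons for withdrawal go into the case report form, and "the last data recorded for these participants will be included in the data analysis".
- Methods, Data collection and analysis (text after Table 1): "Data will be analyzed using the intention-to-treat analysis and will include all participants who will undergo randomization". It adds: "Missing data will be imputed using multiple imputations".

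Two further places show when the permission might be used. The withdrawal section lists grounds for termination that include "3) non-compliance to trial medication, and (4) the request for other medications to relieve the symptoms of FD". The Concomitant medication section says that "the patients can be excluded under the request for other medications to relieve the symptoms of FD".

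On blinding, the Randomization section states: "Both the patients and clinicians will be blinded until the end of the trial".

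**The concern.** An intention-to-treat analysis fixes the analysed set at randomisation. The exclusion permission allows that set to be changed afterwards, by someone who has followed the participant's symptoms, adherence and tolerability. The grounds named nearby are not neutral. A request for other dyspepsia medication is a sign of poor response in the condition that the primary outcome, the NDI-K symptom score, measures. Non-compliance may also be related to response or tolerability.

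If exclusions follow response, the remaining arms are no longer comparable as randomised, and the mean difference no longer estimates the effect in everyone randomised. With 50 participants planned, a few exclusions can matter. The sponsor could then not show that the reported primary result is the intention-to-treat result that the article promises.

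**Working it through.** **1. The statements side by side.** Suppose a randomised participant is taken off observation and the investigator uses the permission on that participant's data.

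| Statement | Are the collected data analysed? |
|---|---|
| Withdrawal section, exclusion permission | No |
| Withdrawal section, next sentence | Yes, the last recorded data |
| Analysis section, intention-to-treat | Yes, the participant is included |

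The first row cannot be met together with the other two. Multiple imputation does not reconcile them, because it fills values that were not observed, whereas the permission concerns values that were.

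**2. The plan's own sample size.** Inputs from Sample size calculation: "The average variation (*δ*) is assumed to be 20", SD 22.4, two-sided 5%, power 80%, allocation 1:1.

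n = 2 × (1.960 + 0.842)² × 22.4² / 20² = 19.69, rounded up to 20 per arm. With 20% dropout, 40 / 0.8 = 50, or 25 per arm. Both figures reproduce, and the point below does not alter them.

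**3. One common rule in both arms, the pattern compatible with blinding.** Assumptions not in the documents: improvement is normally distributed with mean 20 on BST and 0 on placebo, SD 22.4 in each; everyone below a common cut-off c is excluded; selection on outcome is perfect. The cut-off is set so that

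½Φ((c − 20)/22.4) + ½Φ(c/22.4) = the overall fraction excluded.

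The mean of those who remain in an arm with mean μ is μ + 22.4 × φ(a) / (1 − Φ(a)), where a = (c − μ)/22.4.

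| Excluded overall | c | Placebo excluded | BST excluded | Mean left, BST | Mean left, placebo | Difference |
|---|---|---|---|---|---|---|
| 5% | −30.35 | 8.8% | 1.2% | 20.72 | 3.91 | 16.8 |
| 10% | −21.54 | 16.8% | 3.2% | 21.65 | 6.77 | 14.9 |
| 20% | −10.77 | 31.5% | 8.5% | 23.80 | 11.62 | 12.2 |

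If BST works, a rule that ignores the arm still removes mostly placebo participants, and the difference shrinks. If BST has no effect, the two distributions are the same, the rule treats them alike and the expected difference stays at 0. In simulation, removing the 3, 5 or 10 worst of 50 under no effect leaves the two-sided type I error at about 5%.

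**4. Upper bound: exclusions in one arm only.** No true effect, 25 per arm, SD 22.4, Student's t test, 100,000 simulated trials, the k worst outcomes removed from the BST arm alone.

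| k | Bias in favour of BST | Two-sided type I error |
|---|---|---|
| 0 | 0 | 4.9% |
| 1 | 1.8 | 6.5% |
| 2 | 3.4 | 9.3% |
| 3 | 4.9 | 13.4% |
| 5 | 7.5 | 23.8% |

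If exclusion in the BST arm instead follows a variable correlated 0.3 or 0.5 with outcome, three exclusions give a bias of about 1.5 or 2.4 and a type I error of about 5.7% or 6.9%. Five exclusions give about 6.4% or 9.1%.

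The documents give no number of exclusions, so every fraction and every k here is assumed.

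**The case against.** The paragraph can be read kindly. The permission stands next to the power to end observation, the next sentence states retention, and the analysis section agrees with retention. On that reading the phrase only ends participation. This carries some weight: two statements favour keeping the data and one permissive phrase does not. It does not dispose of the point, because ending observation is already named separately, and excluding data is a further act.

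Three stronger readings are tempting, and the documents do not support them.

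- *The false-positive rate could rise to 24%.* That needs perfect selection on outcome in the BST arm alone. Investigators blinded to arm cannot aim for this. Arm-related differences in adherence or tolerability could produce a weaker form, which is why the one-arm figures serve only as an upper bound.
- *Safety data could vanish from the comparison.* The section on evaluation of adverse events requires each event to be recorded in the case report form and all to be assessed for causality. Nothing says that they may be dropped from safety reporting.
- *The lack of exclusion criteria, blinded sign-off or a per-protocol definition is itself a defect.* An article may leave these to the full protocol or SAP. What remains is a conflict between rules that the article does state.

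It is also fair to say that the bias from a common rule is towards no effect, so it costs power and understates benefit rather than creating a false claim.

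**Conclusion.** The conflict is real and lies within the article's own text, so it is not a matter of detail left elsewhere. Blinding limits the harm without removing it. Under one common outcome-related rule, a true difference of 20 falls to about 16.8, 14.9 or 12.2 when 5%, 10% or 20% of participants are excluded, with the type I error near 5%. Inflation arises only if outcome-related exclusions differ between arms. These sizes rest on normal outcomes, the plan's own 20 and 22.4, perfect selection on outcome and assumed numbers of exclusions. They show what the wording permits and do not predict what will happen. Severity: should-fix.

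**What to change.** In the withdrawal section, strike the half of the sentence that permits exclusion of participant data. State instead that all data collected from a randomised participant stay in the intention-to-treat analysis, whatever the reason for ending treatment or observation, except where the participant withdraws consent for use of data already collected. Reword the sentence in Concomitant medication on excluding patients so that it does not imply removal from the analysis; when treatment or observation stops is not at issue here. If an analysis without non-compliant or deviating participants is wanted, make it a supplementary per-protocol set decided under blind.

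The cost is a sentence or two. Sample size, visits and procedures do not change. The article describes the trial as ongoing at submission, so the rule should be settled before unblinding.
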